#### Drop-out analyses

Drop-out analysis is a type of sensitivity analysis where we aim to examine differences between drop-outs and participants of all study groups concerning several descriptive variables (age, gender, BMI, cardiovascular fitness, perceived anxiety level, cognitive function, comorbidity) in order to investigate if the incidence of drop-outs is selective or random.

Outcome data collected prior to an eventual later study discontinuation will be included in the analyses i.e. a participant lacking data from the 1-year follow-up will still have data from the 12-week post-intervention.

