### Assessments

Assessments occur at baseline, post-intervention (after 12 weeks) and at one-year follow-up (Table 1). Participants will be assessed by the study physician, psychologist, psychiatrist and physiotherapist.

**Table 1 Tab1:** Measures, methods and assessment points used in the study

Variable	Measure	Method	T0 Baseline	T1 12 weeks	T2 1 year
Psychiatric diagnosis	M.I.N.I.	Interview	X	X	X
Anxiety symptoms	BAI	Self-report	X	X	X
Depression symptoms	MADRS	Self-report	X	X	X
Psychoactive drugs	Questionnaire	Self-report	X	X	X
Blood pressure	MmHg	Objective assessment	X	X	X
BMI	Kg/m^2^	Objective assessment	X	X	X
Alcohol use	AUDIT	Self-report	X	X	X
Quality of life	EQ-5D	Self-report	X	X	X
Cognitive function	WAIS-IV (d.s., b.d., m.r.)	Objective assessment	X	X	X
Cognitive function	D-KEFS (d.f.)	Objective assessment	X	X	X
Cardiovascular fitness	Åstrand’s ergometer test	Objective assessment	X	X	X
Muscle strength	One-leg-rising-test	Objective assessment	X	X	X
Sick leave	Questionnaire	Self-report	X	X	X
Hormones/cytokines	S-IGF-1, S-BDNF, S-VEGF, CRP	Blood samples	X	X	X

*M.I.N.I.* Mini International Neuropsychiatric Interview, *BAI* Beck Anxiety Inventory, *MADRS* Montgomery Åsberg Depression Rating Scale, *BMI* Body mass index, *AUDIT* Alcohol Use Disorders Identification Test, *EQ-5D* EuroQoL-5 Dimension Questionnaire, *WAIS-IV* Wechsler Adult Intelligence Scale, 4th edition, *d.s*. digit span, *b.d*. block design, *m.r.* matrix reasoning, *D-KEFS* Delis-Kaplan Executive Function System, *d.f*. design fluency, *S-IGF-1* serum insulin-like growth factor 1, *S-BDNF* serum brain-derived neurotrophic factor, *S-VEGF* serum vascular endothelial growth factor, *CRP* high sensitivity C-reactive protein

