### Statistical analysis

Data will be presented using descriptive statistics, including the number of observations, means and standard deviations for continuous variables. For categorical variables, frequencies and percentages will be presented and data analysed using Chi-squared tests. Based on plotted histograms (confirming that the data may be considered as approximately normally distributed), continuous data will be analysed using a univariate general linear model (ANCOVA). In this model, treatment will be used as a categorical independent variable and baseline levels as covariates. Data will be presented as changes of means with corresponding 95% confidence intervals, standard deviations and *p*-values from group comparisons. The categorical outcome “treatment responsive” will be analysed using Chi-squared tests. A p-value below 0.05 will be considered statistically significant for all analyses. All statistical analyses will be performed by a statistician using SAS version 9.4 (SAS Institute, Cary, NC).

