In order to reduce the risk for worsening mental health or symptoms during the study we have a) assessed eligibility for study participation by a physician; b) excluded patients with heightened suicide risk; c) requested participants to contact research personnel if they feel worse; d) as intervention personnel, only included persons with knowledge regarding symptoms of worsening of anxiety and/or depression. If a patient experience worsening of symptoms, the subject will be excluded from the study and put in contact with the treating physician or psychologist. The study physician and physiotherapists will continuously inquire about and record any signs of worsening of mental health symptoms or side-effects.

Another experience from our previous intervention study on depression was the disappointment of being randomized to the control group. Therefore, the patients in the control group will have a single session with a physiotherapist and general advice about physical activity according to public health recommendations as well as a 3-month membership at a training facility for after study completion. Such a control condition, was chosen to potentially feel meaningful and inspiring to the participants. [47] A passive control group such as a wait-list design or treatment as usual are associated with negative influences on study results for nonpharmacological treatments, including a possible overestimation of the intervention effects and limited blinding possibilities. [48] Instead of an active control with an alternative behaviour, the current study has two separate interventions groups with different exercise intensities, a design that allows for comparison effectiveness depending on exercise dose as well as permits blinding for participants. All study participants will be informed about the results from the study, as will all participating professionals and the general medical community. Results will be published in peer-reviewed medical journals and results will be disseminated regardless of the magnitude or direction of effect. When writing manuscripts, ICMJE (International Committee of Medical Journal Editors) guidelines regarding authorship will be followed.

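### The 1-year ANCOVA makes no use of week-12 values when the 1-year visit is missed, and the drop-out comparison is descriptive: it cannot establish that loss is random

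*Protocol article*

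**What the plan says.** The Assessments section sets three visits: "Assessments occur at baseline, post-intervention (after 12 weeks) and at one-year follow-up (Table 1"). BAI and the other continuous outcomes in Table 1 are measured at each of them.

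Under Statistical analysis, "continuous data will be analysed using a univariate general linear model (ANCOVA"), and in that model "treatment will be used as a categorical independent variable and baseline levels as covariates". No visit term, participant effect or week-12 term is mentioned.

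Under Drop-out analyses, "Outcome data collected prior to an eventual later study discontinuation will be included in the analyses". The protocol explains this by saying that "a participant lacking data from the 1-year follow-up will still have data from the 12-week post-intervention". The same section states that "Drop-out analysis is a type of sensitivity analysis where we aim to examine differences between drop-outs and participants of all study groups", on variables such as age, gender, BMI, fitness, perceived anxiety level, cognitive function and comorbidity, "in order to investigate if the incidence of drop-outs is selective or random".

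Under Ethical considerations, if a patient's symptoms worsen, "the subject will be excluded from the study and put in contact with the treating physician or psychologist".

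**The concern.** The statement that partial data are included sits beside a model that can use a week-12 value only in the 12-week comparison. At 1 year the stated model rests on attenders alone, and baseline is all it knows about how attenders differ from those who left. If staying to 1 year is related to how a participant did at week 12, and differently by arm, adjustment for baseline does not remove the resulting bias, although the week-12 values have already been collected.

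The described check does not fill this gap. A sensitivity analysis asks how the treatment effect changes under other assumptions about missing data. This one compares characteristics of two groups and produces no treatment effect. The 1-year contrast, one of the two post-baseline comparisons, is what is at stake.

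**Working it through.** **Inputs.** From the protocol: 60 per arm, SD 9 and a 5-point BAI difference (sample size section), and the ANCOVA terms quoted above. The protocol gives no loss rate and no correlations between visits, so these are assumptions:
- Correlations: baseline with week 12, 0.5; baseline with 1 year, 0.4; week 12 with 1 year, 0.6.
- Loss at 1 year: 10-13% or 26-28%. The planned 25% over-recruitment gives 60 × 1.25 = 75 per arm. If that margin is meant for loss, which the protocol does not say, it covers 1 − 60/75 = 20%, between the two bands.
- Mechanism: in one arm the log-odds of loss rise with week-12 BAI by 0.5 to 1.5 per SD; in the other arm loss is unrelated to it.

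**Who enters which analysis.**

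| Post-baseline data | 12-week ANCOVA | 1-year ANCOVA | 1-year contrast, mixed model |
|---|---|---|---|
| Both visits | in | in | in |
| Week 12 only | in | out | in, through the week-12 value |
| 1 year only | out | in | in |
| Neither | out | out | out |

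Only the second row separates the stated plan from a joint model at 1 year.

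**Size by hand.** Suppose selective loss shifts the mean week-12 BAI of the attenders in one arm by *s* points. With equal SDs, their 1-year mean moves by 0.6*s* and their baseline mean by 0.5*s*. The ANCOVA, with a baseline slope of about 0.4, takes back 0.4 × 0.5*s* = 0.2*s*. The bias left is 0.6*s* − 0.2*s* = 0.4*s*. A bias of 0.2 to 0.7 points thus corresponds to *s* of 0.5 to 1.75, and 0.4 to 1.3 points to *s* of 1.0 to 3.25. If loss is completely random, *s* = 0 and the bias is 0.

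**Size by simulation.** The joint model below uses baseline, week 12 and 1 year together; effects are BAI points in favour of exercise.

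| Scenario | Truth | 1-year ANCOVA | Joint model |
|---|---|---|---|
| One arm, 10-13% lost, no effect | 0 | off by 0.2-0.7 | about 0 |
| One arm, 26-28% lost, no effect | 0 | off by 0.4-1.3 | about 0 |
| One arm, slope 1 | 0 | 0.92 | 0.00 |
| One arm, slope 1 | 2.5 | 3.28 | 2.49 |
| Both arms, slope 1 | 5 | 4.75 | 5.03 |

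The slope-1 rows have 26-29% lost; there the SD of the estimate was 1.70-1.74 for the ANCOVA and 1.67-1.70 for the joint model, so the joint model costs no precision. Against the 5-point target, the bias range is 0.2/5 = 4% to 1.3/5 = 26%. Loss of poor responders from the exercise arm flatters exercise; loss of good responders does the reverse.

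A second set of assumptions (baseline with each follow-up 0.5, week 12 with 1 year 0.7, truth 5) marks the limits:
- 25% loss completely at random: ANCOVA 4.95 (SD 1.66), joint 4.96 (SD 1.59). Only a little precision is at issue.
- Loss in the exercise arm depending on the unseen 1-year score: ANCOVA 6.96, joint 6.29. The joint model removes (6.96 − 6.29)/(6.96 − 5) = 0.67/1.96, about a third of the bias.

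**What the drop-out comparison can detect.** With 180 participants and 20% lost (36 against 144), power to detect a true difference of 0.3, 0.4 or 0.5 SD in a measured variable is 36%, 57% or 76%. When loss depended on the unseen 1-year score in the exercise arm, a comparison of baseline BAI was significant in about 5% of runs, as under random loss. Comparing week-12 BAI does better when that is what drives loss: at slope 1 in the exercise arm and 25% loss, it was significant in about 84% of trials within that arm and 54% pooled over arms; at slope 0.5, in 36% within the arm.

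**The case against.** Baseline-adjusted ANCOVA at each visit is a standard and valid analysis. The article condenses a fuller plan, and the SAP is not shown. Imputation and tipping-point analyses commonly sit there, so their absence is not held against the protocol. What stands is narrower: the model the article does state has no place for week-12 values at 1 year, and the article does give the drop-out comparison a label and a purpose.

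Several stronger readings are tempting, and the documents do not support them.
- *Week-12 data are thrown away.* They are not; they enter the 12-week analysis. That each visit has its own model is itself an inference from the word univariate and the listed terms.
- *The drop-out comparison cannot detect loss related to response.* The protocol does not restrict perceived anxiety level to baseline, and week-12 BAI is available. Used that way, the comparison is informative, as the detection rates show.
- *A non-significant comparison will be read as proof of random loss.* The protocol says only that it will investigate the question.
- *Outcome-related loss at 1 year is certain, because patients who worsen are removed.* The removal rule links some loss to symptoms, but its frequency and timing are not given. If removal precedes week 12 there is no week-12 value, and the mixed model recovers nothing.

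The sizes also depend on chosen inputs. Even 0.92 is only about half of the estimate's own SD (0.92/1.74 = 0.53), and with no true effect and the same mechanism in both arms the bias is about 0.

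**Conclusion.** The point holds for the 1-year contrast only. Under the stated ANCOVA, a participant who misses 1 year contributes nothing to it despite a week-12 value. If attendance depends on week-12 response differently by arm, the bias is about 0.2 to 0.7 BAI points at 10-13% loss and 0.4 to 1.3 points at 26-28% loss, and about 0 if loss is completely random. These figures rest on 60 per arm, SD 9, correlations of 0.5, 0.4 and 0.6 and dependence in one arm; loss rates, correlations and mechanism are assumptions, so they illustrate and do not predict. A reader might infer that the trial's 1-year result will be biased; the documents do not show that, since they report neither how much loss occurs nor what drives it.

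The drop-out comparison can reveal that loss is related to measured variables. It cannot establish that loss is random and it re-estimates no effect, so the sensitivity-analysis label is wrong. This is a cheap improvement to a workable plan rather than a fault that invalidates it.

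**What to change.** Estimate the 12-week and 1-year contrasts for BAI and the other repeated continuous outcomes from one mixed model for repeated measures, with arm by visit, baseline by visit and unstructured covariance, in all randomised participants with any post-baseline value. State this in place of the univariate ANCOVA, so that the promise to include earlier data also holds at 1 year. Keep the drop-out table, describe it as descriptive, include week-12 values for those lost afterwards, and delete the wording that calls it a sensitivity analysis or suggests that it can settle whether loss is random.

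The cost is plan wording and modest programming in the SAS version already named, with no new data. The limit should be written down too: the model removes bias only when loss depends on observed data, not when it depends on the unseen 1-year score or when removal comes before week 12.

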#### Health-economic analyses

Health-economic analyses will be performed using primary data generated within the project concerning health-related quality of life effects associated with the intervention and information about healthcare resources utilized. A health-economic model that depicts the clinical trial will be constructed and used for computing cost-utility measures. Moreover, the model will be constructed for performing extensive probabilistic sensitivity analyses [44, 45].

### Project timeline

Recruitment started in May 2017 and will continue until March 2020. The trial is divided into one pilot set and five trial sets and the estimated primary completion date is June, 2021 (Fig. 2).

**Fig. 2 Fig2:**
[figure not shown]
Study timeline

### Ethical considerations

The study is approved by the regional Ethics Committee in the Gothenburg, Sweden, National Board of Health prior to start (300–16) prior to start.

Interested patients are informed verbally and in writing about the aims and the study design including randomization, the importance of active participation for reliable data but also about the possibility to withdraw from the study at any time without disadvantages. Each participant has to sign a statement of informed consent, delivered by the study physician, before study inclusion.

All data collected will be coded and anonymized. A key connecting serial numbers with personal identification numbers will be stored and locked away. All analyses will be performed on coded data presented on group levels. The database will be password-protected, encrypted and stored for 10 years in a locked, fireproof archive at Gothenburg University, designed for such purposes. All participating researchers will have access to the database. Collected blood samples will be destroyed after the completion of the study. A Data Protection Officer (DPO) has been assigned and reported to the Swedish Data Protection Authority.

The current research team has previously performed an intervention study on the effects of exercise on depressed patients [46] and hence anticipates low risk of complications. A small risk for injury while exercising exists, such as a sprained ligament or a strained muscle. In order to minimize the risk for injuries, exercise programs are developed and modified according to the ability of each patient by experienced primary care physiotherapists. Moreover, ECG is monitored before the intervention and individuals with a pathological ECG will be excluded, which will minimize the risk for cardiac side-effects during exercise.

In order to reduce the risk for worsening mental health or symptoms during the study we have a) assessed eligibility for study participation by a physician; b) excluded patients with heightened suicide risk; c) requested participants to contact research personnel if they feel worse; d) as intervention personnel, only included persons with knowledge regarding symptoms of worsening of anxiety and/or depression. If a patient experience worsening of symptoms, the subject will be excluded from the study and put in contact with the treating physician or psychologist. The study physician and physiotherapists will continuously inquire about and record any signs of worsening of mental health symptoms or side-effects.

Another experience from our previous intervention study on depression was the disappointment of being randomized to the control group. Therefore, the patients in the control group will have a single session with a physiotherapist and general advice about physical activity according to public health recommendations as well as a 3-month membership at a training facility for after study completion. Such a control condition, was chosen to potentially feel meaningful and inspiring to the participants. [47] A passive control group such as a wait-list design or treatment as usual are associated with negative influences on study results for nonpharmacological treatments, including a possible overestimation of the intervention effects and limited blinding possibilities. [48] Instead of an active control with an alternative behaviour, the current study has two separate interventions groups with different exercise intensities, a design that allows for comparison effectiveness depending on exercise dose as well as permits blinding for participants. All study participants will be informed about the results from the study, as will all participating professionals and the general medical community. Results will be published in peer-reviewed medical journals and results will be disseminated regardless of the magnitude or direction of effect. When writing manuscripts, ICMJE (International Committee of Medical Journal Editors) guidelines regarding authorship will be followed.

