### Intervention

Using computer generated randomisation (http://www.randomizer.org), patients are randomized into three groups: 1) Intervention I: 12-week exercise program with low-intensity training 3 times per week for 45 min; 2) Intervention II: 12-week exercise program with moderate to high-intensity training 3 times per week for 45 min; 3) Control group: a single physiotherapy session with general advice about physical activity. Participants are then informed by phone if they belong to an intervention group or the control group. Both intervention groups include cardiorespiratory and resistance training, and participants in group II are also encouraged to perform an additional running session per week. Participants in the control group are encouraged to start exercising after the study is completed and also receive a 3-months membership at a training facility, but are discouraged of actuating other exercise programs during the trial. All three groups self-report physical activity during the study. For participants in the intervention groups, the study physiotherapists designed individualized exercise programs during a one-to-one session with the patients on one occasion. The exercise program is designed as a circuit training with 12 stations, repeated twice (45 s workout, 15 s for transportation between stations and 1 min rest between the two laps). It also includes 10 min of warm-up exercises and 5–10 min of cool down and stretching exercises. Cardiorespiratory exercises include step-ups, lunges, jump rope, burpees, step touches side-to-side and step-touches on step board. Resistance training exercises include squats, abdominal plank position, hip lifts, crunches, row exercises and push-ups. Participants in intervention group I and II exercise separately in group sessions in the gym with the physiotherapist according to a predetermined schedule. A pulse-watch and the Borg RPE scale are used to monitor level of exertion to ensure appropriate exercise intensity. For intervention group I, the intensity level corresponds to 1.5–2.9 metabolic equivalents (METs), a Borg rated perceived exertion (RPE) of 10–14 and a maximal heart rate of 40–59%. The corresponding figures for intervention group II are 3.0–8.9 METs, Borg RPE 12–17 and 60–94% of maximal heart rate. Patients who are unable to participate in a session perform replacement exercises on their own.

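### Between baseline and week 12, side effects and transient worsening are looked for far more often in the exercise arms than in controls, so the recorded events would tend to under-count controls

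*Protocol article*

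**What the plan says.** The monitoring rule stands under Ethical considerations: "The study physician and physiotherapists will continuously inquire about and record any signs of worsening of mental health symptoms or side-effects". The article gives no frequency of inquiry for any arm. The same section asks participants to get in touch if they feel worse, and says that a participant whose symptoms worsen is excluded from the study and referred back to the treating clinician.

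The Intervention section fixes how often the physiotherapists meet each arm. The first arm is a "12-week exercise program with low-intensity training 3 times per week for 45 min" and the second a "12-week exercise program with moderate to high-intensity training 3 times per week for 45 min". Participants in both "exercise separately in group sessions in the gym with the physiotherapist according to a predetermined schedule", and the physiotherapists also design "individualized exercise programs during a one-to-one session with the patients on one occasion". The third arm is listed as "Control group: a single physiotherapy session with general advice about physical activity". Missed sessions are made up alone: "Patients who are unable to participate in a session perform replacement exercises on their own".

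On measurement, "Assessments occur at baseline, post-intervention (after 12 weeks) and at one-year follow-up". The study physician, psychologist, psychiatrist and physiotherapist take part in these assessments. Table 1 schedules M.I.N.I., BAI and MADRS at all three points and has no row for injury or side effects. Under Blinding, the physiotherapists are the only staff who know the allocation; the study physicians are listed as blinded.

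**The concern.** A single monitoring rule works differently by arm when its users meet the arms at very different rates. A strain, or a bad fortnight of anxiety, in an exercise participant can come up at the next training session, days later. In a control it surfaces only if it falls near the single session, lasts until week 12, is recalled then, prompts the participant to call, or comes up in some physician contact that the article does not schedule. The staff with the extra contact also know the allocation.

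At stake is the meaning of the recorded side effects and worsening. If these logs were later used to say how well exercise was tolerated relative to control, part of any excess in the exercise arms would come from looking more often. Transient worsening in controls during the 12 weeks is also less likely to be noticed.

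**Working it through.** The article gives no figure for harms, so there is nothing to reproduce. The check is a count of contacts, followed by an illustration on assumed inputs.

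**Scheduled contacts per participant** (Intervention and Assessments sections)

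| | Exercise arms | Control |
|---|---|---|
| Group sessions | 12 × 3 = 36 (maximum) | 0 |
| Individual physiotherapy session | 1 | 1 |
| Week-12 assessment | 1 | 1 |
| Total after baseline, to week 12 | up to 38 | 2 |
| Adding the baseline and one-year assessments | up to 40 | 4 |

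The figure of 36 is a ceiling, because missed sessions are done alone. The difference lies entirely in the group sessions. The two exercise arms have the same schedule as each other.

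**What unequal contact could do to the counts.** Assumptions, none of them from the article:
- the true rate of events is equal in all arms;
- onset is uniform over weeks 0 to 12, and an episode lasts D weeks;
- exercise participants have every episode recorded;
- a control's episode is recorded if still present at week 12 (probability D/12), and otherwise with self-report probability s; the single control session is ignored.

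Control detection = D/12 + (1 − D/12) × s, and apparent risk ratio = 1 / control detection.

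| D (weeks) | s | Control detection | Apparent risk ratio |
|---|---|---|---|
| 2 | 0 | 0.17 | 6.0 |
| 2 | 0.25 | 0.167 + 0.833 × 0.25 = 0.38 | 2.7 |
| 2 | 0.50 | 0.58 | 1.7 |
| 2 | 0.75 | 0.79 | 1.3 |
| 8 | 0 | 0.67 | 1.5 |
| 8 | 0.75 | 0.92 | 1.1 |
| 12, or s = 1 | any | 1.00 | 1.0 |

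**Chance of a spurious p < 0.05**, if someone tested 120 exercise participants against 60 controls (60 per arm, from the sample size section) with an assumed true rate of 20%. The normal approximation is Φ[(difference − 1.96 × SE under the null) / SE under the alternative].
- D = 2, s = 0.25: recorded 20% against 0.20 × 0.375 = 7.5%. Φ[(0.125 − 1.96 × 0.0577) / 0.0499] = 0.59.
- D = 2, s = 0.75: recorded 20% against 15.8%. The same formula gives about 0.09.

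The effect thus ranges from large to none, and the two quantities that decide it, episode duration and self-report, are not in the article.

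**The case against.** The strongest reply is that the article plans no comparison of harms between arms. None appears in the aims, Table 1 or the statistical analysis section, and the quoted sentence sits among measures to protect participants. That stands: the point limits how the recorded events may be used and does not show an error in a planned analysis.

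It can also be said that the study physician's inquiry is not restricted to any arm and may reach controls between visits, at a frequency the full protocol may set. That too stands as a possibility. It does not cancel the asymmetry in physiotherapist contact, which the article states.

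A reader might infer more than this, in three ways.
- *That staff see controls only once.* They do not. Controls attend all three assessments, where both recording roles take part; the physiotherapists run the ergometer test there; and every participant is asked to call if worse.
- *That every comparison of harms is biased.* M.I.N.I., BAI and MADRS follow the same schedule in all arms, and the two exercise arms have equal scheduled contact. Table 1 lacks a common item for injury or side effects, but it does have common measures of symptom worsening. The self-report questionnaire also covers concurrent illnesses, though its wording is not shown.
- *That detection can be multiplied out by contact.* With an assumed 5% chance per contact, 36 sessions give 1 − 0.95^36 = 84%, against 5% for one. The 5% has no source, self-report is set to zero, the week-12 visit is left out, and a complaint open to detection at all 36 sessions would still be there at week 12.

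Finally, the programme itself carries a risk of injury, as Ethical considerations acknowledges, so some true excess in the exercise arms is to be expected. That is a reason to ascertain injuries equally, since otherwise the true excess cannot be separated from the excess due to closer observation.

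**Conclusion.** The point holds in a limited form. Between the scheduled assessments, ascertainment of side effects and transient worsening is unequal by design: up to 37 physiotherapist contacts (36 + 1) in the exercise arms against one in controls. Wherever recording depends on contact, the direction is under-counting in controls. The size cannot be stated. The range of apparent risk ratios from 6.0 to 1.0 illustrates assumed inputs and is not an estimate.

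The low versus moderate-to-high intensity comparison is not affected by this contact difference. Worsening measured by M.I.N.I., BAI or MADRS is also unaffected, but only among those assessed. Because detected worsening leads to exclusion, and the drop-out section speaks of keeping data collected before discontinuation, unequal detection could influence who reaches the week-12 assessment. A reader might go on to infer that the efficacy result is biased. The article does not say how many participants would be excluded or whether their outcomes would still be collected, so that does not follow from it.

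The change is worth making because it is cheap. It leaves the efficacy design as it is.

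**What to change.** 1. Add the same short self-completed items (injury, other health events, and worsening since the last visit) to the questionnaires that all arms complete at week 12 and one year. Self-completion matters: if a blinded physician took the history, a report of an injury during training could reveal the allocation. For the same reason, keep the answers away from the outcome assessors.
2. Base any exercise-versus-control statement on harms on these items and on the proportion with BAI or MADRS above baseline, both of which are already collected. Report complaints logged at training sessions separately, for the exercise arms only.
3. Optionally, send all three arms the same brief check-in on the same dates, through the letter, telephone and text-message channel already used for reminders, so that detection before week 12 is more alike.
4. Reconcile the text on monitoring and on exclusion for worsening with the assessment schedule.

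Cost: a few questionnaire items and, if step 3 is adopted, a few messages, which add some contact to the control condition. Look-back items miss some minor events, so the compared counts will be lower than the session logs. Recruitment began in May 2017, so week-12 visits already held cannot be recovered; later week-12 visits and the remaining one-year visits can carry the items.
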